**Fig. 1 Fig1:**
[figure not shown]
Recruitment Flowchart for KPIC. Questionnaire: administered at baseline, Year 1 and Year 3 for all who indicated interest and consent to follow up at baseline. Clinical Assessments: will be repeated for early Knee Pain (and new knee pain cases from the no knee pain groups). No repeat assessments will be undertaken for the establish Knee Pain group

#### Year 1 follow-up

### Questionnaire

Of those participants who indicated interest and consent to follow-up at baseline, a follow-up postal questionnaire will be issued in year 1. The year 1 questionnaire will follow the format of the baseline questionnaire with some changes. We will not re-administer questions on constitutional risk factors such as early knee alignment and 2D4D ratio since these would not change from baseline. We will add a set of questions on sleep from the Medical Outcome Survey. A modified body pain mannequin (see Additional file 2) with two questions on symptom severity and widespread pain index will also be included to allow scoring of fibromyalgia as a diagnosis with binary (present/absent) classification using a validated tool [47]. The questionnaire will also be updated to include the Life Orientation Test (LOT) which evaluates a lack of positive beliefs as well as low negative beliefs [48] and a short item test on conscientiousness (Big 5) [49]. We will also add an illness perceptions questionnaire to measure patient’s belief about their KP [50]. These validated tools will be included as they contribute to the psychosocial aspects of the disease and could be predictors of patient and clinical outcomes. All questionnaire changes will be approved following feedback and review from PPI groups and subsequently, submitted for NREC approval.

### Clinical assessment

From the responders to the Year 1 questionnaire, any new cases of early KP (incident KP for most days in a month for the past 12 months) will be identified and invited for clinical assessments as per the baseline protocol. It is estimated that the new incident KP cases may number from *n* = 70–110 from the Year 1 questionnaire mail-outs (based on an annual incidence of 3.2%) [23].

For those early KP participants who attended the baseline appointment, there will be repeat assessments of muscle strength, gait, balance and ultrasound. The PPT assessments will be done on the most painful knee of participants with KP. For those who have an equal pain severity in both knees, the right knee will be assessed. The PPT protocol will also be complimented by TS testing. TS or windup will be used to assess central sensitivity and characterise central pain processing abnormalities by measuring how pain is perceived (using a NRS) once repetitive stimuli (weighted pinprick) is applied [51, 52].

#### Year 3 follow-up

A follow-up questionnaire will also be mailed out at Year 3. Only the early KP group (including incident KP identified at year 1) will be re-assessed at year 3 for change of outcomes. In addition, people without KP at baseline or year 1 but reporting KP at year 3 will be considered as new incident KP cases and will be assessed clinically (including knee radiographs) as per the baseline protocol.

### Sample size

The sample size calculated was based on the primary objective of this study: to examine the natural history of KP within a community setting which involves the recruitment of as many knee pain positive and knee pain negative individuals with detailed exposure data captured from the questionnaire. The subsequent objectives are to examine the incidence, progression and associated risk factors.Source population: 40,000 questionnaires will be sent via post with a target of recruiting 10,000 participants (response rate 25%), which will form the source population of this study. Based on our previous studies, this would give 2500 people with knee pain (KP +) and 7500 people without knee pain (KP -). The sample size is 10 times larger than the subsequent sample size calculations for incidence, progression and risk factors of KP.Sample size for incidence and progression of KP: A sample of 730 participants will allow the detection of 3% (±1%) annual incidence of knee pain in a population over the age of 45^24^ at power of 90% (alpha 0.05, two-sided). This sample will also be able to detect a 14% occurrence of knee pain progression (worsening) (±5%) 24 at a power of 90% (alpha 0.05). An annual drop off rate of 30% plus 3% annual incidence rate of KP is excluded from the source population.Risk factors: A logistic regression model was used to calculate the sample size for one primary risk factor and multiple covariates. According to the annual incidence of 3% KP^24^ and an OR of 2 associated with overweight/obese [53] and assuming a multiple correlation coefficient of other covariates is 0.3, 702 participants are required for this risk factor analysis to give a power of 90% (alpha 0.05). For progression (i.e., 14% KP worsening), however, 203 participants are required.

### Sub-studies sample sizes

Sample size for NP: According to a NP prevalence of 28% (±8) based on a previous community population sample [15], 85 participants are required to yield a power of 90% (alpha 0.05).

Sample size for PPT: According to a difference of 0.32 SD (standard deviation) on pressure pain threshold (PPT) between established KP (group ii) and No KP [54] and 0.16 SD between early KP and no KP, 600 participants are required for a three-group comparison with an unbalanced (400:100:100 for the “Early KP”, “Established KP” and “No KP”) one-way ANOVA design. This unbalanced design will be applied to keep the main interest on early KP and its subsequent follow-up for progression.

Sample size for US: Data from a previous Nottingham community based case control study was used and this study [55] comprised four groups: people with KP and radiographic changes (Kellgren and Lawrence (K&L) score ≥ 2); people with KP without radiographic changes; people with no KP but radiographic changes; and people with no KP and normal x-rays. We used KP only as “early KP”, KP plus radiograph changes as “established KP” and combined the two no KP groups to form the control. We then calculated standardised effect sizes for each case group versus control based on means/SD (1.06, 2.02 and 0.96, respectively). The total sample size required is 80 (group balance 40:20:20) which will yield 90% power with 5% type I error for this unbalanced multiple group case-control study.

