### Clinical assessment

From the questionnaire responders, a sample of participants who indicated a willingness to consider undergoing knee radiographs and other assessments will be identified. Three distinct groups of participants (early KP, established KP and no KP) will then be identified based on their questionnaire responses on KP duration and severity. They will be sent a letter of invitation together with a participant information sheet. Those who reply registering their interest and who give contact details will undergo an additional telephone screening prior to being booked into a single hospital appointment. The inclusion criteria for clinical assessment are:

i. Participants with recent-onset KP (*n* = 200) are defined as mild/moderate and/or intermittent KP occurring for the first time in the past 3 years for most days of at least one month, unrelated to obvious major trauma.

Once, the early KP group is recruited, participants from the established KP (ii) and no KP group (iii) will be age and gender matched to this early KP group (i) using the following inclusion criteria:

ii. Participants with established persistent KP (*n* = 100): defined as KP for over 3 years which has been moderate (NRS >6) and/or persistent for most days of the past 3 months, unrelated to obvious major trauma.

iii. Participants with no KP: defined as no KP (n = 100) within the past 5 years.

Respondents to the questionnaire who report total knee joint replacement surgery or major prior knee injury will be excluded - only those with spontaneous (“primary”) KP will be selected for groups (i) and (ii).

Participants will be asked to attend their hospital appointment fasting since the previous evening (for purposes of blood and urine biomarker collection).. They will be verbally informed about the assessments by trained research personnel, regarding the nature and purpose of the study, invited to voice any questions or concerns, and given time to decide whether or not to participate. Written informed consent will then be obtained from all study participants prior to any assessment (one copy being given to the participant) and all data will be treated as confidential and anonymised.

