#### Reproducibility

For reproducibility of assessments, we will use the kappa-statistic for categorical data (x-rays and dichotomous US data) and the concordance correlation coefficient for continuous data. The magnitude of agreement on categorical data will be measured using the unweighted kappa statistic (for binary) or the weighted kappa statistics (for ordered categorical data) [56]. A numerical rating of kappa will be interpreted according to accepted criteria (0–0.2: slight; 0.2–0.4: fair; 0.4–0.6: moderate; 0.61–0.8: substantial; 0.81–1.0: almost perfect) and 95% confidence intervals will be reported [57]**.**

All analyses will be undertaken using Stata Statistical Software: Release 13 (StataCorp. 2013, College Station, TX: StataCorp LP). *P* values less than 0.05 will be considered significant.

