There are some limitations to the study design of KPIC. Firstly, being a questionnaire-based cohort study, the design is prone to a number of biases including response bias (participants with KP more likely to respond to the questionnaire) and recall bias (participants with KP may recall events and exposures more accurately compared to those without KP). However, the question on KP is very specific and focused on any symptoms in and around the knee for most days of at least one month in the previous 12 months which is the ‘gold standard’ for epidemiological research studies [30]. Current knee pain was defined as pain in or around the knees for most days of the past one month for incident knee pain. This was different from early onset knee pain which was defined as knee pain (ever or current for most days of at least a month) in the past 3 years. However, due to the transient nature of knee pain, it is possible that the baseline questionnaire might not allow us to correctly identify participants as being knee pain positive or knee pain negative (misclassification bias). A self-reported questionnaire approach also ensures the absence of interview bias from the study results [23]. Secondly, although the questionnaire cohort is large (*n* = 40,000), the clinical subset cohort is relatively small (*n* = 400). There may be limitations to using multiple adjusted effect estimates that have all been taken from a single logistic regression model. A bias otherwise known as the table 2 fallacy could occur where the interpretation of the confounder estimates may be different than for the exposure effect estimates [65]. Thirdly, there is a selection bias associated to a potential differential loss to follow-up in the group with moderate-severe pain or participants who are frail. The responders and non-responders will be compared at Year 1 and Year 3 in order to measure and subsequently adjust for this bias.

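### The PPT sub-study is sized at 600 (400:100:100) while the clinical cohort is planned at 400 (200:100:100), and the 600 does not follow from its stated effects: both layouts give about 51% omnibus power

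*Protocol article*

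**What the plan says.** All references are to the protocol article.

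- **Sub-studies sample sizes, PPT paragraph.** The planning effects are given as "According to a difference of 0.32 SD (standard deviation) on pressure pain threshold (PPT) between established KP (group ii) and No KP" and "0.16 SD between early KP and no KP". From these the authors conclude that "600 participants are required for a three-group comparison with an unbalanced (400:100:100 for the" early, established and no-KP groups respectively, with the test named as a "one-way ANOVA design". The imbalance is justified by the interest in early KP and its later progression. The paragraph states neither power nor alpha. The neuropathic pain paragraph just before it does state both: "85 participants are required to yield a power of 90% (alpha 0.05".
- **Clinical assessment (baseline).** The early group is half that size: "Participants with recent-onset KP (*n* = 200) are defined as mild/moderate and/or intermittent KP". The established and no-KP groups are 100 each. PPT is measured at this clinical visit.
- **Discussion, limitations.** The total is confirmed: "the clinical subset cohort is relatively small (*n* = 400".
- **Year 1 and Year 3 follow-up.** New incident KP cases are to be assessed as at baseline. An estimated 70 to 110 are expected at Year 1; no number is given for Year 3.
- **Reproducibility.** The general significance level is set: P "values less than 0.05 will be considered significant". The Statistical analysis section uses the same threshold.

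**The concern.** There are two separate problems. First, the sample size section asks for 400 early-KP participants in a comparison for which the recruitment section supplies 200. Second, the required number looks wrong on its own terms. A one-way ANOVA gains little from enlarging the middle group when the other two lie at equal distances on either side of it, and that is the pattern the planning effects describe.

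What is at stake is how a PPT result is read. Someone who takes the sample size paragraph at face value will assume that 600 was both adequate and planned. If the omnibus test is then non-significant, the result may be taken as evidence that thresholds do not differ by KP status. Under the authors' own effects, such a result would occur about half the time even though the differences exist.

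**Working it through.** **Inputs**

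- Means in SD units relative to no KP: none 0, early 0.16, established 0.32 (Sub-studies sample sizes). Both differences are taken to run in the same direction.
- Group sizes: 400:100:100 (Sub-studies sample sizes) and 200:100:100 (Clinical assessment, Discussion), in the order early : established : none.
- Alpha 0.05, from Statistical analysis and Reproducibility, because the PPT paragraph gives none.
- Power: not stated for PPT. Results are shown for 80% and 90%; 90% is the figure wherever the article does state a power for a sample size.

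**Formula.** For a one-way ANOVA with k = 3 groups and SD = 1, the noncentrality is λ = Σ nᵢ(μᵢ − μ̄)², where μ̄ = Σ nᵢμᵢ / N. Power is P(F′(2, N − 3, λ) > F₀.₉₅(2, N − 3)).

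**Step 1. Try to reproduce the 600 as stated (400:100:100).**

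μ̄ = (400 × 0.16 + 100 × 0.32 + 100 × 0) / 600 = 96 / 600 = 0.16

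λ = 400 × 0² + 100 × 0.16² + 100 × 0.16² = 2.56 + 2.56 = 5.12

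The critical value F(2, 597) is 3.011, so power = **51.2%**. The 600 is not reproduced at 80% or 90%.

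**Step 2. The cohort actually planned (200:100:100).**

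μ̄ = (200 × 0.16 + 100 × 0.32) / 400 = 64 / 400 = 0.16, so λ is again 5.12.

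The critical value F(2, 397) is 3.018, so power = **51.1%**. A simulation of 5,000 runs per layout gave 51.1% for both.

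**Step 3. Add the Year 1 incident cases.** Early groups of 200 + 70 = 270 and 200 + 110 = 310 leave λ at 5.12 and power at 51.1%. Both remain short of 400.

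**Step 4. What would be needed** (alpha 0.05, same effects):

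| Allocation | 80% power | 90% power |
|---|---|---|
| 4:1:1 | 1,134 (756:189:189) | 1,488 (992:248:248) |
| 2:1:1 | 756 (378:189:189) | 992 (496:248:248) |
| 1:1:1 | 570 | 747 |

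A balanced 200:200:200 has λ = 2 × 200 × 0.16² = 10.24 and power 82.3%. This is the nearest match to 600 at alpha 0.05, but it is not the stated design.

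**Step 5. Detectable effect at 200:100:100.** 90% power needs both differences multiplied by about 1.58: 0.32 × 1.58 = 0.51 SD and 0.16 × 1.58 = 0.25 SD.

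**Step 6. Pairwise comparisons** (two-sided t-test, unadjusted). Established versus none, 100:100 at 0.32 SD: 61%. Early versus none at 0.16 SD: 26% with 200:100 and 30% with 400:100.

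**Step 7. Sensitivity to the assumptions.**

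- At alpha 0.10, power is about 64% in both layouts.
- If the two differences ran in opposite directions, power would be 98% at 400:100:100 and 95% at 200:100:100. The 4:1:1 design would then need only 312 (80%) or 408 (90%), so 600 is still not recovered.
- Two alpha 0.10 variants come within 3% of 600: 608 at 2:1:1 for 80% and 618 at 1:1:1 for 90%. Neither uses the article's significance level or the stated allocation.

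**The case against.** The strongest reply has four parts.

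*No power claim is contradicted.* The PPT paragraph names no power, so the shortfall is measured against a target that the reader supplies. This stands as a limit on the wording: the documents do not claim 90% for PPT and then miss it. But calling a number required implies some adequate target, and about 51% is not one by any usual convention.

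*The 400 may be cumulative.* Incident cases at Year 1 and Year 3 are assessed as at baseline, the Year 3 section counts Year 1 incident cases with the early group, and the imbalance is linked to follow-up. So 400 could describe a later time point and need not be a plain slip. That is possible, but nothing says so. The Year 1 estimate reaches 310 at most, the Year 3 number is not given, and a larger early group would not raise the omnibus power. The remedy should therefore be to reconcile the sections, without presuming which figure governs.

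*Extra early-KP participants are not wasted.* They lift early versus none slightly (26% to 30%) and support the study of progression, which is the stated reason for the imbalance. This is correct; the lack of gain concerns the omnibus test under these planning means.

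*It is a sub-study.* The primary objective rests on a target of 10,000 questionnaire respondents, and the Discussion already lists the small clinical subset as a limitation. This stands and lowers the severity.

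A reader might also infer that PPT is the study's main measure of central sensitisation, so that a central objective fails. The article does not say so. It assigns central sensitivity to temporal summation from Year 1, and also uses painDETECT and a body pain mannequin. A reader might likewise conclude that a linear trend test should become the primary PPT analysis. The article does not support that either: it plans multinomial logistic regression with no KP as reference, and a trend test would reach only about 62% under the planning means.

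**Conclusion.** The point holds in two parts. The conflict between 600 (400:100:100) and 400 (200:100:100) is on the face of the text and needs no statistical assumption. The second part, that 600 does not follow from the stated effects, rests on three assumptions: both KP groups differ from no KP in the same direction, alpha is 0.05, and the target is a conventional 80% to 90%. The first is the natural reading, since 0.16 is half of 0.32 and the Background speaks of reduced thresholds; the second is the article's general level; the third is inferred.

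On that footing, omnibus power is about 51% at either layout. The stated 4:1:1 design would need roughly 1.9 times (1,134 / 600) to 2.5 times (1,488 / 600) the stated number.

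The 51% is the power of the ANOVA used for sizing, not of the adjusted multinomial model planned for the baseline clinical data. It is tempting to say that the authors computed 600 for equal groups and then reallocated it. The 82% at 200:200:200 is compatible with that, but the documents do not show it.

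This should be fixed. It concerns a sub-study, and the primary sample size is untouched.

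**What to change.** 1. Reconcile the PPT group sizes across Clinical assessment, Year 1 and Year 3 follow-up, Sub-studies sample sizes and the Discussion. If the 400 early-KP participants are meant to include later incident cases, say so, and give the time point and the expected number.
2. Replace the statement that 600 are required with the size actually planned. Give either its omnibus power for 0.32/0.16 SD (about 51%) or its detectable effect (about 0.51/0.25 SD at 90% power for 200:100:100), and state the alpha, the power and the assumed direction of both differences.
3. Add a sentence that a non-significant three-group PPT result is not evidence of equal thresholds at this size.

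The cost is text only. Recruitment, assessments and analysis need not change; the stated figure becomes less favourable.

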### Statistical analysis

#### Questionnaire and clinical assessments

For baseline questionnaire data, prevalence of KP and type of KP (e.g., NP) will be estimated. Risk factors associated with KP and different types of KP (e.g., NP) will be examined. Odds ratio (OR) and 95% confidence interval (CI) will be given to present the association and logistic regression model will be used to adjust for confounding factors such as age, gender, body mass index and pain severity.

For the baseline clinical assessment data, the overall difference among three groups categorised according to KP status (Early KP, established KP and controls) will be analysed using multinomial logistic regression. This is an extension of binary logit regression when the categorical dependent variables have more than two response categories. The “No KP” group will be chosen as a reference (base). As cases and controls will be frequency matched (by age and gender) unconditional logistic regression analysis will be chosen. The odds ratio (OR) and 95% CI will be used to measure an association. All models will be adjusted for potential confounding factors and checked for interactions and collinearity as appropriate.

The loss to follow-up rate (from baseline to Year 1 and then to Year 3) can be measured in terms of variables such as age, gender and severity of symptoms and in order to mitigate the differential bias, a multiple imputation model alongside sensitivity analyses will be considered. For follow-up data, incidence and progression of KP will be estimated. Logistic regression model will be used for year 1 and other single time point follow-up analysis. The Kaplan–Meier method will be used to generate survival curves and a log-rank test will be used to examine the time-to-event outcomes for multiple follow-up data. The proportional hazards assumption will be examined graphically using the Kaplan–Meier method for each risk factor. The Cox proportional hazards model will be used to calculate the hazard ratio (HR), adjusted for confounding factors such as age, gender and BMI. Differences between the study population; those invited to participate and responders will be tested using a one-way analysis of variance (ANOVA) with post hoc Bonferroni correction. Statistical significance will be inferred when *P* value is less than 0.05, or when the 95% confidence interval (CI) does not include unity.

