### Participants

Inclusion criteria: all men and women aged 40 years and over, located on the General Practitioner (GP) register, irrespective of KP status.

Exclusion criteria: inability to give informed consent, terminal or severe mental illness, and pregnant women (for clinical assessments only).

Eligibility will be decided by the health professionals in each general practice using the GP register. The GP register is a log of patients who have registered with their local National Health Service practice, who have lived in the local area (minimum of 24 h) and who have free access to primary care regardless of nationality or immigration status. Regional general practices will be approached via the Clinical Research Network (East Midlands) including Nottinghamshire and Derbyshire. A postal questionnaire will be sent to approximately 40,000 adults. The baseline questionnaire will be accompanied by a covering letter from their general practitioner (GP) introducing the study and the objectives. Participants will be able to read about the study and if willing, complete the questionnaire and return it in an enclosed pre-paid envelope to Academic Rheumatology (University of Nottingham) at Nottingham City Hospital. Return of a completed questionnaire will be taken as implicit consent. At the end of the questionnaire responders will be asked to indicate separately whether or not they would be willing to: (1) receive further information about a single visit to Academic Rheumatology to undergo knee radiographs and other assessments; (2) receive a further similar postal questionnaire in one year’s time; and (3) to receive further information of other future studies related to knee pain and OA.

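### The baseline representativeness check applies one-way ANOVA to overlapping groups, so its test is conservative; it should compare responders with non-responders

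*Protocol article*

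**What the plan says.** The mailing is described under Participants: "A postal questionnaire will be sent to approximately 40,000 adults". The Sample size section adds "40,000 questionnaires will be sent via post with a target of recruiting 10,000 participants (response rate 25" per cent, and from those replies "this would give 2500 people with knee pain (KP +) and 7500 people without knee pain (KP" negative).

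Under Statistical analysis (Questionnaire and clinical assessments), representativeness is to be examined as follows: "Differences between the study population; those invited to participate and responders will be tested using a one-way analysis of variance (ANOVA". The procedure is a "one-way analysis of variance (ANOVA) with post hoc Bonferroni correction", and significance is declared when the P "value is less than 0.05, or when the 95% confidence interval (CI) does not include unity". The sentence names no variables and does not define the study population.

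For baseline data the same section says that "prevalence of KP and type of KP (e.g., NP) will be estimated". It mentions neither weighting nor a crude estimate. The Objectives set the general population as the target for phenotype prevalence. The Discussion names "response bias (participants with KP more likely to respond to the questionnaire") as a limitation. The adjustments that the article describes are multiple imputation with sensitivity analyses, to be considered for loss to follow-up, and a comparison of responders with non-responders at Years 1 and 3.

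**The concern.** One-way ANOVA and its pairwise follow-up tests assume that each person belongs to one group only. Here every responder is also counted among those invited. The two group means are then positively correlated, and the ordinary formula overstates the standard error of their difference. The test rejects too rarely, which in a representativeness check is the reassuring direction. The Discussion treats representativeness as important, so a check that leans towards passing deserves correction.

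A significance test at this sample size also says little about how large a difference is, and it supplies no correction. That matters because three quarters of those mailed are expected not to reply and the article itself predicts which way this would tilt the knee pain figures, yet the adjustment it sets out concerns later attrition. ANOVA would also be the wrong tool for a categorical register variable such as gender, if gender is among those compared.

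**Working it through.** **Inputs.** Invited: 40,000 (Participants; Sample size). Response: 25% (Sample size). Expected knee pain among responders: 2500 of 10,000 (Sample size). Alpha: 0.05, taken as two-sided (Statistical analysis). Relative response of people with knee pain: not given, so assumed between 1.1 and 2.

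**The plan's own figures.** 40,000 × 0.25 = 10,000 responders, leaving 30,000 non-responders; 10,000 × 0.25 = 2500 with knee pain. Both stated figures are reproduced.

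**Standard errors, in SD units.**
- Assumed by ANOVA for responders minus invited: √(1/10,000 + 1/40,000) = 0.0112.
- True value when responders are contained in the invited: √(1/10,000 − 1/40,000) = 0.0087.
- Responders minus non-responders (disjoint groups): √(1/10,000 + 1/30,000) = 0.0115.

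As mean(responders) − mean(invited) = 0.75 × [mean(responders) − mean(non-responders)], and 0.75 × 0.0115 = 0.0087, the nested contrast with its correct standard error is the same test as the disjoint one. Only the assumed standard error is at fault.

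**Actual size.** The test rejects when the difference exceeds 1.96 × 0.01118. In true standard errors that is 1.96 × 0.01118/0.00866 = 2.53, which gives a two-sided size of 0.011 instead of 0.05. At the Bonferroni level for three pairs (0.05/3 = 0.0167) the size is 0.0020. In 2000 simulated null data sets the overlapping two-group test rejected in 0.0135 and the disjoint test in 0.0495. With three nested groups and an assumed study population of 80,000, the overall ANOVA rejected in 0.006.

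**Detectable responder versus non-responder difference, 90% power.**
- Disjoint: (1.96 + 1.2816) × 0.01155 = 0.037 SD.
- Overlapping: (1.96 × 0.01118 + 1.2816 × 0.00866)/0.75 = 0.044 SD.
- With Bonferroni for three pairs: 0.042 and 0.050 SD.

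Power without Bonferroni, by true difference:

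| Difference | Disjoint | Overlapping |
|---|---|---|
| 0.03 SD | 0.74 | 0.53 |
| 0.04 SD | 0.93 | 0.83 |
| 0.05 SD | 0.99 | 0.96 |
| 0.10 SD | 1.00 | 1.00 |

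**Prevalence (secondary).** If people with knee pain reply r times as often as others, observed odds = r × true odds. For an observed 25% (odds 1/3), the true odds are 1/(3r):

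| r (assumed) | True prevalence | Upward bias, points |
|---|---|---|
| 1.1 | 23.3% | 1.7 |
| 1.25 | 21.1% | 3.9 |
| 1.5 | 18.2% | 6.8 |
| 2 | 14.3% | 10.7 |

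The sampling 95% half-width is 1.96 × √(0.25 × 0.75/10,000) = 0.0085, or 0.85 points.

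**The case against.** The strongest reply is that the contrast itself is sound. A reader might infer from the factor 0.75 that the check hides a quarter of the non-response difference. That does not follow: the non-response bias of a mean is exactly the responder mean minus the invited mean, so 0.75 belongs to the quantity of interest. This reply stands, and it leaves only the standard error at fault.

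Second, the consequence is small. A shift in detectable difference from 0.037 to 0.044 SD will rarely change a conclusion, and any difference of 0.10 SD is found either way. This also stands.

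Third, the wording is loose. The study population is undefined, and the invitation could be the one to the clinical assessment. In that case the figures for 10,000 of 40,000 do not apply. The groups would still overlap, because clinic invitees are drawn from questionnaire responders and those who accept are among the invitees. If non-responders were meant, the sentence should say so, as the Discussion does for Years 1 and 3.

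Fourth, a reader might infer that prevalence will be reported unweighted. The article does not say that. It condenses a fuller protocol, and the analysis plan and the additional file on representativeness are not shown. The response ratios above are also assumptions: the Discussion describes a risk of response bias and gives no size. If phenotype prevalence is expressed among people with knee pain only, a common response ratio cancels. These limits confine the prevalence part to a suggestion.

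**Conclusion.** The point holds for the test. The article fixes a method that needs independent groups and applies it to groups that overlap. On the postal reading, with 10,000 replies from 40,000 and a common SD, the responder-versus-invited comparison has a size of about 0.011 instead of 0.05. The check therefore leans towards declaring responders representative, with a modest practical loss.

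The documents do not support a claim that the check would miss a material imbalance, or that the plan commits to a crude prevalence. What they do show is that the stated adjustment is directed at follow-up losses, while the larger baseline non-response, with its predicted direction, has none attached to it in the article. The range of 23.3% to 14.3% for an observed 25% illustrates why that matters against a sampling half-width of 0.85 points. It rests wholly on the assumed ratios of 1.1 to 2 and does not estimate the bias.

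**What to change.** Replace the ANOVA sentence with a comparison of responders and non-responders, two mutually exclusive groups, on the variables held on the practice register. Report standardised differences with confidence intervals, and use chi-square for any categorical variable such as gender. If the study population is meant as a further group, define it.

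As a secondary change, state how baseline non-response enters the prevalence estimates. Show prevalence standardised to the invited register by age and sex beside the crude figure, and add a sensitivity range over assumed knee pain response ratios. The range is needed because age and sex weighting cannot remove a tendency to reply that depends on knee pain itself.

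The cost is a change of analysis wording and a little more work. The planned comparison already needs register data on everyone invited, from which the non-responders follow by subtraction. Standardised estimates will have slightly wider intervals. No planned sample size changes.
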